**Figure 2 figure2:**
[figure not shown]
Overview of user centred design process.

**Figure 3 figure3:**
[figure not shown]
Study timeline.

### Description of Test Sites

There will be 3 sites in 3 trial countries: Belgium, Norway, and Portugal. With these countries, a large coverage of the European context is achieved, allowing to study cultural, social, economic, and legal differences between the countries and European regions.

The test site in Belgium will be Aan de Beverdijk care home based in Hamont-Achel. This care home is part of the VULPIA group, a care provider that comprises 22 elderly care homes. Aan de Beverdijk focuses on providing tailored care based on the individual needs of its 90 residents. The test site in Norway will be Odda sjukeheim, a municipality-based care home for the elderly based in the center of Hardanger. The test site in Portugal will be the Lar Santa Joana Princesa care home for the elderly. This care home is a part of the Santa Casa de Misericórdia de Lisboa (SCML). SCML operates according to a humanitarian goal, and its care homes focus on promoting the quality of life of its residents.

Although it is inevitable that there will be differences among care homes, the SENSE-GARDEN space at each site is being custom-built for the specific purposes of this project. Each SENSE-GARDEN will have the same equipment, the same software and will be in a closed, private room. Having a controlled space at each test site will help reduce the amount of variability among the 3 countries.

### Participants

This study will recruit a total of 55 PWDs living in care facilities, in a multisite trial with 3 sites. Details for each site are as follows: (1) Belgium—1 study site, 25 PWDs, 25 informal caregivers, and 3 professional caregivers, (2) Norway—1 study site, 15 PWDs, 15 informal caregivers, and 3 professional caregivers, and (3) Portugal—1 study site, 15 PWDs, 15 informal caregivers, and 3 professional caregivers.

### Recruitment

Participants will be recruited at each study site by a professional caregiver from the SENSE-GARDEN team. The caregivers will inform potential participants about the study with the use of an information leaflet about the project. The potential participants who are interested in the study can then voluntarily express their willingness to participate. The participants who do not express an interest will not be contacted by the project team.

Professional caregivers included in the study will have at least 6 months experience in caring for dementia patients and a background in either nursing, occupational therapy, or physiotherapy or another relevant background when supported by long-term professional experience as a caregiver.

Before the study, the professional caregiver will have a 1-week training in SENSE-GARDEN use. This training comprises guidance on how to collect information from the participant and/or their family members for creating a user profile, upload media contents to the SENSE-GARDEN system, create *workflows* of media contents for individual SENSE-GARDEN sessions, and control the numerous elements in the SENSE-GARDEN space.

Each potential participant will undergo an assessment by a health professional for the evaluation of inclusion and exclusion criteria. For the participants fulfilling the criteria, a randomization to the intervention or control group will be performed.

#### Inclusion Criteria

To be included in the study, the participant must be aged ≥55 years and living with dementia in stage 2 (moderate) or stage 3 (severe) according to the Clinical Dementia Rating (CDR) Scale [22], possibly with comorbidities. The participant must also provide informed consent to participate (self-given or given by nominated legal tutor).

#### Exclusion Criteria

Other severe psychiatric disturbance diagnosed by Diagnostic and Statistical Manual of Mental Disorders (4th Edition, Text Revision) criteria, concurrent severe medical condition (extreme or disabling comorbidities), or physical disability not allowing participation in the SENSE-GARDEN activities.

#### Informal Caregivers

The informal caregiver should be a family member or close friend of the PWD. There will be at least 1 informal caregiver for each PWD recruited.

##### Inclusion Criteria

There is no age limit for the informal caregivers; they should have a computer and internet connection and provide signed informed consent to participate.

### Study Procedures

During the 3 months of the intervention period, the PWD will visit the SENSE-GARDEN on an average of 3 times per week. Each participant should visit the SENSE-GARDEN a minimum of 25 times during the intervention period. Any participant who visits less than 25 times will be considered a dropout. On each visit to the SENSE-GARDEN, the PWD is accompanied by 1 caregiver (formal or informal). It is desirable that approximately one-third of the visits are performed with an informal caregiver.

Logs of interaction with the system will be collected continuously, including visit time and duration and system feedback given by the caregivers (through a tablet interface).

Observations will be made at 3 of the SENSE-GARDEN sessions during the intervention period. During this time, measurements on social presence and physical activity will be collected. Video recording will be required during the 3 observation sessions. The recordings will solely be used for data analysis and will not be shared. They will be accessible only to authorized researchers in charge of data analysis. Video recordings will only be made during sessions involving participants that have given their informed consent to being recorded.

For the control period, visits from the family will be logged during normal care.

### Assessment Methods

The methods include the following types of data collection: self-reported measures, questionnaires, interviews, and observations. For interviews and questionnaires requiring the participation of the PWD, the capacity of the PWD to provide information will be considered. In the case of participants that are not competent to provide input, the tests will be performed with a proxy who will provide information on the patient’s behalf. In some cases, the presence of both the PWD and proxy will be considered.

#### Screening Measures

The CDR Scale [22] will be used to assess the severity and progression of the individual’s dementia. Only individuals at level 2 (moderate dementia) or level 3 (severe dementia) will be included in this study.

To decide how to best tailor the SENSE-GARDEN intervention to each individual participant, the Adolescent/Adult Sensory Profile will be used [23]. The Adolescent/Adult Sensory Profile is a tool that evaluates behavioral responses to sensory experiences, with categories focusing on taste and smell, touch, auditory processing, visual processing, movement, and activity level. This measure has recently been tested with people with severe dementia to identify individual sensory processing preferences [24]. This tool will be used in the SENSE-GARDEN study to determine the most appropriate level of sensory stimulation for each participant.

#### Outcome Measures

The following measures will be applied at baseline (T0), 4-week follow-up (T1), 12-week follow-up (T2), and a final follow-up at 16 weeks (T3). An overview of these measures is given in Table 1.

**Table 1 table1:** Overview of outcome measures.

Outcome		Measurement	Timepoint
**Outcome for the person with dementia**			
	A reduction in BPSD^a^	CMAI^b^ and BANS-S^c^	T0^d^, T1^e^, T2^f^, T3^g^
	Improvement in quality of life	QUALID^h^	T0, T1, T2, T3
	Reduction in depressive symptoms and loneliness	CSDD^i^	T0, T1, T2, T3
	Increase in the feeling of social presence	OERS^j^, OME^k^, VNVIS-CR^l^	T1^m^, T2^m^, T3^m^
	Improvement in cognitive function	Mini-Cog^n^, FAST^o^, GDS^p^	T0, T1, T2, T3
	Relief from feelings related to the care burden	Semistructured interview	T3
	Increase in self-awareness and engagement	Audio recordings analyzed using conversation analysis	T1^m^, T2^m^, T3^m^
	ICF^q^ scores	WHODAS 2.0^r^	T0, T1, T2, T3
	Prescription of medication	Medical records	T0, T1, T2, T3
	Mortality rate compared with previous existing records	Medical records	T0, T1, T2, T3
	Number of hospitalizations comparing control and intervention groups	Medical records	T0, T1, T2, T3
	Exploration of physiological data including electrodermal activity and heart rate	Empatica E4 wristband	T1^m^, T2^m^, T3^m^
	Improvement in physical function and balance	FRT^s^	T0, T1, T2, T3
**Outcome for the informal caregiver**			
	A reduction in caregiver burden	ZBI^t^	T0, T1, T2, T3
	Improvement in caregiver coping and relief from stress	Brief-COPE^u^	T0, T1, T2, T3
	An increased quality of visits to the person with dementia	FAVS-D^v^	T0, T1, T2, T3
	An improvement in the quality of relationship with the person with dementia	QCPR^w^	T0, T1, T2, T3
**Outcome for the formal caregiver**			
	Reduction in caregiver burnout	MBI-HSS^x^	T0, T1, T2, T3

^a^BPSD: behavioral and psychological symptoms of dementia.

^b^CMAI: Cohen–Mansfield Agitation Inventory.

^c^BANS-S: Bedford Alzheimer Nursing Scale–Severity.

^d^T0: baseline.

^e^T1: 4-week follow-up.

^f^T2: 12-week follow-up.

^g^T3: 16-week follow-up.

^h^QUALID: Quality of Life in Late Stage Dementia scale.

^i^CSDD: Cornell Scale for Depression in Dementia.

^j^OERS: Observed Emotion Rating Scale.

^k^OME: Observational Measurement of Engagement.

^l^VNVIS-CR: Verbal and Nonverbal Interaction Scale.

^m^Measurement to be taken during SENSE-GARDEN session.

^n^Mini-Cog: 3-min instrument to screen for cognitive impairment in older adults.

^o^FAST: Functional Assessment Staging Tool.

^p^GDS: Global Deterioration Scale.

^q^ICF: International Classification of Functioning, Disability and Health.

^r^WHODAS 2.0: World Health organization Disability Assessment Schedule 2.0.

^s^FRT: Functional Reach Test.

^t^ZBI: Zarit Burden Interview.

^u^Brief-COPE: abbreviated version of the Coping Orientation to Problems Experienced inventory, a self-report questionnaire.

^v^FAVS-D: Family Visit Scale for Dementia.

^w^QCPR: Quality of Carer Patient Relationship scale.

^x^MBI-HSS: Maslach Burnout Inventory–Human Services Survey.

##### Person With Dementia

###### Primary Outcomes

####### A Reduction in Behavioral and Psychological Symptoms in Dementia

The Bedford Alzheimer Nursing Scale–Severity (BANS-S) [25] and the Cohen–Mansfield Agitation Inventory (CMAI) [26] will be used to determine whether the intervention reduces behavioral and psychological symptoms of dementia. BANS-S is a nursing staff–administered questionnaire that assesses dressing, sleeping, speech, eating, mobility, muscles, and eye contacts in persons with severe dementia. It is a reliable measure with good internal consistency (Cronbach alpha=.64-.80). CMAI is a widely used tool that evaluates aggressive behavior, nonaggressive behavior, and verbally aggressive behavior. The caregiver-rated questionnaire comprises 29 agitated behaviors, each rated on a 7-point scale of frequency ranging from 1 (never) to 7 (several times an hour).

####### Increase in the Feeling of Social Presence

Observational measures will be used to determine the level of social engagement in the participants with dementia. These tools will be the Observed Emotion Rating Scale (OERS) [27], the Verbal and Nonverbal Interaction Scale (VNVIS-CR) [28], and the Observational Measurement of Engagement (OME) [29]. All 3 measures have previously been used in studies observing people living with dementia. OERS assesses pleasure, general alertness, anxiety or fear, and sadness at 10-min intervals. VNVIS-CR is a tool developed specifically to measure verbal and nonverbal interaction in people with mild to moderate dementia. The 26 items assess nonverbal social behaviors, nonverbal unsociable behaviors, verbal sociable behaviors, and verbal nonsociable behaviors. The OME evaluates various dimensions of engagement in people with mild to severe dementia. The tool measures attention to stimulus, attitude toward stimulus, rate of refusal, duration, and activity.

Observations will be made during at least 2 of the SENSE-GARDEN sessions for each participant. For participants in the intervention group, recordings will be taken during a SENSE-GARDEN session in week 4, week 12, and week 16. Participants randomized to the control group will only have recordings taken during a session in week 4 and week 12, as these individuals will no longer be visiting the SENSE-GARDEN after week 12.

####### Improvement in Cognitive Function

The Mini-Cog [30], the Functional Assessment Staging Tool (FAST) [31], and the Global Deterioration Scale (GDS) [32] will be used to assess whether there is any improvement in cognitive function among the participants. The Mini-Cog is an assessment of cognitive function that only takes 2 to 5 min to complete. It comprises a word recall task and a clock drawing test. FAST is a dementia staging tool that focuses on an individual’s level of functioning and ability to carry out activities of daily living. Scores range from 0 to 7, with a higher score indicating an increased level of functional decline. GDS is a brief dementia staging scale that assesses the stage and progression of dementia in terms of cognitive decline. Scores range from 0 to 7, with a higher score indicating a more severe level of cognitive decline.

####### Increase in Self-Awareness and Engagement

Conversation analysis will be used to assess the PWD’s level of self-awareness and engagement with both the SENSE-GARDEN stimuli and the caregiver conducting the session. To conduct conversation analysis, audio recordings of certain SENSE-GARDEN sessions will be taken.

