### Primary Outcomes

The study will examine 2 quantitative and 2 qualitative primary outcomes for the PWD, namely, reduction in behavioral and psychological symptoms in dementia (BPSD), improvement in cognitive function, increase in the feeling of social presence, and an increase in self-awareness and engagement. The primary outcomes for the informal caregiver (family caregivers) are a reduction in carer burden, improvement in carer coping and relief from stress, an increased quality of visits from the informal caregivers to the PWD, and an improvement in the quality of the relationship with their relative with dementia. The primary outcome for the professional caregiver is a reduction in caregiver burnout.

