### Data Analysis

Quantitative data will be analyzed using SPSS Statistics version 25 (IMB Corp). Stratification by gender, age, and type and stage of dementia will be used to analyze the data. Repeated measures analysis of variance (ANOVA) will be used to assess whether the SENSE-GARDEN intervention has an effect on participants over time. Given the novelty of the SENSE-GARDEN intervention, it is not possible to assess the previous literature for clinically meaningful differences. However, Cohen *d* has been used to determine effect size in studies focusing on the effects of nonpharmacological interventions on behavioral outcomes in PWDs [43].

Cohen *d* is a measure of standardized difference between 2 means [44]. It uses standard deviation units to express the magnitude of difference between the 2 means, indicating the importance of the difference. Cohen has defined a small effect size as *d*=0.2, a medium effect size as *d*=0.5, and a large effect size as *d*=0.8.

For this study, repeated measures ANOVA will be performed on the data using SPSS to assess the effects of the intervention over the numerous time points (T0-T3). We estimate that a sample size of 55 will have over 80% power to detect a medium difference between means at a .05 significance level.

Qualitative interview data will be analyzed using thematic analysis [45]. Thematic analysis is a method of identifying patterns of prevalent ideas or responses and can offer rich insight into the attitudes and beliefs of participants. This aspect of the study will be vital for understanding the users’ experiences of the SENSE-GARDEN.

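### Two of the four primary outcomes for the person with dementia are stated as an increase but are first recorded in week 4, in session, so only a within-exposure week 4 to 12 change can be described for everyone

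*Protocol article*

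**What the plan says.** The Introduction, under Primary Outcomes, states: "The study will examine 2 quantitative and 2 qualitative primary outcomes for the PWD". Two of the four are an "increase in the feeling of social presence, and an increase in self-awareness and engagement".

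The opening sentence of Outcome Measures is general: "The following measures will be applied at baseline (T0), 4-week follow-up (T1), 12-week follow-up (T2), and a final follow-up at 16 weeks (T3". In Table 1, however, the rows for these two outcomes list T1, T2 and T3 only, each with footnote m: "Measurement to be taken during SENSE-GARDEN session". Every other primary outcome in the table has T0 to T3. These are behavioral and psychological symptoms, cognitive function, the four informal-caregiver outcomes and professional burnout.

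The Methods text on social presence agrees with the table rows. For the intervention group, "recordings will be taken during a SENSE-GARDEN session in week 4, week 12, and week 16". For the others: "Participants randomized to the control group will only have recordings taken during a session in week 4 and week 12". For self-awareness and engagement, "audio recordings of certain SENSE-GARDEN sessions will be taken", and no recording outside sessions is mentioned.

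Study Design gives the intervention to all participants for 3 months. Data Analysis plans repeated measures ANOVA for quantitative data, to "assess the effects of the intervention over the numerous time points (T0-T3". Study Procedures provides for observation at three sessions during the intervention period.

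**The concern.** An increase needs something to increase from. For these two outcomes the first value comes after roughly a month of sessions, and no one has a value before exposure, at the first session or outside a session. Nor does a comparison group fill the gap. Both groups are exposed to week 12, and controls have no recording at week 16, so the only randomised contrast in the trial (weeks 12 to 16) is not available for these outcomes.

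Two errors of interpretation could follow. A benefit present from the first sessions would show as no increase between weeks 4 and 12. Conversely, a rise between weeks 4 and 12 could reflect growing familiarity with the room and the facilitator, or the increasing personalisation that the Introduction describes. The outcome as worded could not tell these apart.

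**Working it through.** **1. Schedule, section against section.**

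| Source | What it gives for the two outcomes |
|---|---|
| Outcome Measures, opening sentence | T0, T1, T2, T3 |
| Table 1 rows and footnote m | T1, T2, T3, in session; no T0; no distinction by group |
| Text on social presence | weeks 4, 12, 16 (intervention); weeks 4, 12 (control); at least 2 sessions |
| Text on self-awareness and engagement | audio of certain sessions |
| Study Procedures | 3 observed sessions during the intervention period |
| Data Analysis | T0-T3 repeated measures ANOVA, for quantitative data |

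The specific rows and text agree with each other, and both differ from the general opening sentence. Primary outcomes for the person with dementia with a T0: 2 of 4. Without: 2 of 4. Measurements per participant for the latter: 3 (intervention) or 2 (control), against the 4 that a T0-T3 analysis uses. Table 1 lists T3 for both groups, although controls have no session to measure in after week 12.

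**2. Exposure before the first value.** Study Procedures gives an average of 3 visits per week.
- Expected visits in 12 weeks: 3 × 12 = 36.
- Visits in 4 full weeks: 3 × 4 = 12, which is 12/36 = 33% of those expected and 12/25 = 48% of the 25-visit minimum.
- A session held during week 4 follows at least 3 × 3 = 9 visits, so the range is about 9 to 12.

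**3. The plan's power figure.** Data Analysis claims over 80% power for a medium difference (d = 0.5) with 55 participants at .05. A paired t test, two-sided (sidedness assumed), has noncentrality 0.5 × √55 = 3.71 on 54 degrees of freedom and power 95.4%. The claim therefore reproduces on a within-subject reading.

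**4. What starting at week 4 could cost (rating scales only).** Assume a true week 0-12 change of 0.5 SD of change, and the same SD of change for weeks 4-12. The remaining standardised change is 0.5 × the share of the gain that falls after week 4. The documents give no time course, so all three below are assumptions.

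| Assumed time course | Share after week 4 | Standardised change | Power, n=55 |
|---|---|---|---|
| Quadratic (late gain) | 1 − (4/12)² = 89% | 0.444 | 90% |
| Linear | 1 − 4/12 = 67% | 0.333 | 68% |
| Half of the remaining gain every 2 weeks | (0.984 − 0.750)/0.984 = 24% | 0.119 | 14% |

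In the last row, 0.750 = 1 − 0.5² (two half-times by week 4) and 0.984 = 1 − 0.5⁶ (six by week 12).

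**The case against.** *The outcomes are qualitative.* The article speaks of two quantitative and two qualitative primary outcomes without saying which are which, and these two are the likely qualitative pair. The ANOVA is described for quantitative data, and nothing says that conversation analysis enters it. A reader might infer that the T0-T3 ANOVA fails for both outcomes. The documents support that only for OERS, OME and VNVIS-CR, which are rating tools. The label does not remove the main point, since a qualitative claim of increase also needs a reference.

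*The construct exists only in session.* Engagement with the SENSE-GARDEN stimuli has no value before the first session, so a true T0 is impossible for part of what is measured. This stands for conversation analysis and largely for OME. It is weaker for OERS and VNVIS-CR, which could be scored in usual care. It explains why T0 is absent, but not why the first observation waits until week 4.

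*The power loss is speculative.* This stands. A reader might take 14% or 68% as the power of this plan. Those figures rest on front-loaded or linear gains, whereas increasing personalisation would point to later gains and about 90%. None of them has a meaning for conversation analysis.

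*A first-session recording is not a baseline.* This also stands. It is exposed, it carries novelty, and it has no unexposed comparator.

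*The three sessions in Study Procedures may simply be weeks 4, 12 and 16.* This is possible for the intervention group. But Study Design sets the intervention period at 3 months, and only weeks 4 and 12 fall within it. The count has to be reconciled on either reading.

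**Conclusion.** The point holds for the stated claim and the measurement schedule. As written, the plan cannot show an increase from any starting point for 2 of the 4 primary outcomes for the person with dementia. None of the 55 participants has a scheduled first-session or pre-exposure value on the specific schedule. The general T0 sentence conflicts with that schedule, and for the three rating scales so does the T0-T3 ANOVA.

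The outcomes are not uninformative: in-session level and the week 4-12 change under exposure can still be described for everyone, with week 16 in addition for the intervention group. The conclusion rests on comparing sections and needs no assumption about effect size. The power range of about 14% to 90% is illustrative. It depends on the assumed 0.5 SD week 0-12 change, on a constant SD of change and on the time course, and it applies to the rating scales only.

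**What to change.** 1. Reconcile Study Procedures, the opening of Outcome Measures, Table 1, the text on social presence and Data Analysis on when, and in which group, these two outcomes are measured. Mark T3 in Table 1 as intervention group only for in-session measures, and give the rating scales an analysis over the time points that they have.
2. Use the third in-period observation in Study Procedures to record each participant's first SENSE-GARDEN session. Score it with the same scales and apply the same conversation analysis. Call it an early-exposure reference, and define the outcome as in-session change from the first session to week 12.
3. State that this change carries novelty and familiarity effects and has no unexposed comparator.
4. Recruitment has begun, so some first sessions may already have passed. Where the first session cannot be recorded, rename the outcome as in-session level and week 4-12 change.
5. In either case, do not claim an increase caused by the intervention.

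Cost: on the week 4, 12 and 16 schedule, one added recording per participant, with its scoring, of a kind already planned; this stays within the three in-period observations that Study Procedures allows. The reconciliation and renaming are changes of wording only.
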